### Patient safety

An independent researcher will analyze the number of study arm switches when the first 20 patients have 6 months of follow-up data. If more than ten patients need to switch to the DAS-guided arm because of discordant treatment decisions for three consecutive months, inclusion will be stopped. The patients who have been included up to that moment will continue to be followed-up, to obtain sufficient information for the evaluation of the HandScan functionality in tight-control treatment strategy. If more than 20% of the first 20 patients have protocol violations based on clinical judgment within 6 months after inclusion, the medical research ethics committee (MREC) will be informed and protocol modifications deemed necessary will be communicated with the site investigators, treating rheumatologists, and, if necessary, trial participants. All adverse events reported by trial participants or observed by investigator staff will be recorded. As the study does not involve experimental medication or treatment, no safety analysis will be performed and an independent data safety and monitoring board will not be installed.

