## Methods/design

This is an investigator-initiated, multi-center, double-blind non-inferiority randomized controlled trial (RCT) of 18 months duration. Patients will be randomized (1:1) to a HandScan-guided treatment aimed at HandScan remission (HandScan arm) or a clinically DAS-guided treatment aimed at ACR/EULAR 2011 Boolean remission (DAS arm). The study is performed at six departments of rheumatology in the Netherlands, the University Medical Center Utrecht (UMCU), and five non-university hospitals: Meander Medical Center Amersfoort, Noord West Ziekenhuizen Alkmaar, Máxima Medisch Centrum Eindhoven, and Gelre Ziekenhuizen Apeldoorn. The study has been approved by the Ethical Committee of the University Medical Center Utrecht, Utrecht, The Netherlands on April 6, 2017 (NL50026.041.14), and has been registered in the Dutch Trial Register (NTR6388). Privacy of patients will be protected according to the General Data Protection Regulation, using anonymized data.

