### Randomization

Randomization lists per center will be prepared at UMC Utrecht, using *nQuery Advisor* in permuted blocks of 4; randomization lists are safeguarded at the UMC Utrecht. Randomization data will be incorporated in the decision-making software application that is used in each of the institutes. This way, on-site research staff, patients, and sponsor trial personnel will remain blinded to treatment strategy. A patient will be allocated to the HandScan or DAS arm, as soon as baseline clinical data are entered into the software application. A patient-specific study number and the year of birth will function as identifiers. Unblinding will not be necessary as both arms receive identical medication in an open fashion.

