### Prevention of under- and overtreatment in the HandScan arm

Since treatment guidance by the HandScan is a novel approach, measures are taken to prevent large deviation of the HandScan-guided strategy from the DAS guided strategy to avoid under- or overtreatment. If treatment decisions dictated by HandScan at three consecutive monthly visits (Fig. 3) are discordant with decisions that would have been dictated by DAS, patients will be switched to the DAS-guided arm and medication decisions will be immediately guided by this arm. Discordancies are tracked in the software application; the switch is implemented without intervention of the researcher, blinded for researcher and patient. This way, patients in the HandScan arm might potentially be under- or overtreated (based on DAS guidance) only for a maximum of two consecutive months.

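### The rule for stopping inclusion needs more than ten arm switches, but only about ten of the first 20 patients can switch

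*Protocol article*

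**What the plan says.** The Patient safety section sets the look: "An independent researcher will analyze the number of study arm switches when the first 20 patients have 6 months of follow-up data". The next sentence gives the threshold: "If more than ten patients need to switch to the DAS-guided arm because of discordant treatment decisions for three consecutive months", in which case inclusion stops and patients already in the trial continue follow-up.

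Three other sections determine who can be counted:

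- Methods/design: "Patients will be randomized (1:1) to a HandScan-guided treatment aimed at HandScan remission" or to DAS-guided treatment.
- Randomization: "Randomization lists per center will be prepared at UMC Utrecht, using *nQuery Advisor* in permuted blocks of 4".
- Prevention of under- and overtreatment in the HandScan arm: after three consecutive discordant monthly decisions, "patients will be switched to the DAS-guided arm and medication decisions will be immediately guided by this arm". The Discussion confirms that this applies to patients in the HandScan arm. No switch out of the DAS arm is described.

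The Patient safety section also says that there will be no safety analysis and no data safety and monitoring board.

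**The concern.** The threshold reads like a majority rule, ten being half of 20. But the numerator can come only from the HandScan arm, while the 20 patients come from both arms. With about ten patients at risk of switching, a count above ten means roughly more than all of them.

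Individual patients are still protected, because the software moves each discordant patient to DAS guidance. What is at stake is whether the trial can answer its question. Under Primary outcome analyses, the intention-to-treat comparison keeps switched patients in the HandScan arm although DAS guides their treatment. That pulls the arms together, and in a non-inferiority trial it favors a non-inferiority conclusion. The per-protocol analysis drops switchers, so with heavy switching few HandScan patients would remain. Heavy switching is therefore what an early look should detect, and this rule would let recruitment continue through it.

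**Working it through.** **Inputs from the article.** Look at the first 20 patients and a threshold of more than ten, i.e. at least 11 switches (Patient safety). 1:1 allocation; six departments stated, five named (Methods/design). A separate list per center in permuted blocks of 4 (Randomization). Switching only from HandScan to DAS (Prevention of under- and overtreatment; Discussion).

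**Assumed.** The article gives no switch rate, so the probability *p* that a HandScan patient switches by 6 months is varied from 30% to 100%, independently between patients. Recruitment is spread over 5 or 6 centers.

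The article gives no derivation or operating characteristics for the threshold, so there is no figure of its own to reproduce.

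**Step 1: HandScan patients among the first 20 (H).** Each complete block contributes exactly 2 HandScan patients of 4. Only incomplete blocks move H away from 10. With one center, 20 is five full blocks, so H = 10 and the rule cannot fire. Simulation (100,000 runs per scenario):

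| Centers | Mean H | SD | P(H ≥ 11) |
|---|---|---|---|
| 5, equal recruitment | 10.0 | 1.02 | 30.5% |
| 6, equal | 10.0 | 1.13 | 32.3% |
| 6, uneven (40/20/10/10/10/10%) | 10.0 | 1.14 | 32.7% |

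The largest possible H with six centers is 16, so firing is improbable but not impossible.

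**Step 2: probability that the rule fires.**

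P(fires) = Σ over h ≥ 11 of P(H = h) × P(Binomial(h, p) ≥ 11)

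Worked example with 6 equal centers and p = 0.8. From the simulation, P(H ≥ 11) = 0.3231, P(H ≥ 12) = 0.0848 and P(H ≥ 13) = 0.0107. Hence P(H = 11) = 0.2384 and P(H = 12) = 0.0741.

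- H = 11, all must switch: 0.8^11 = 0.0859; contribution 0.2384 × 0.0859 = 0.0205
- H = 12, at least 11 switch: 12 × 0.8^11 × 0.2 + 0.8^12 = 0.2749; contribution 0.0741 × 0.2749 = 0.0204
- H ≥ 13, treated as 13: 0.5017; contribution 0.0107 × 0.5017 = 0.0054
- Sum: 0.0463, or 4.6%

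| Assumed switch rate | 5 centers | 6 centers | Simple randomization (for comparison) |
|---|---|---|---|
| 30% | 0.0002% | 0.0002% | 0.004% |
| 50% | 0.04% | 0.05% | 0.4% |
| 70% | 1.1% | 1.3% | 5.3% |
| 80% | 3.9% | 4.6% | 12.8% |
| 90% | 11.8% | 13.3% | 24.9% |
| 100% | 30.5% | 32.3% | 41.2% |

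Uneven recruitment over six centers changes little: 4.7% at an 80% switch rate and 32.7% at 100%.

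**Step 3: the same idea with HandScan patients as the denominator.**

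| Assumed switch rate | At least 11 of 20 HandScan patients | At least 6 of 10 HandScan patients |
|---|---|---|
| 30% | 1.7% | 4.7% |
| 50% | 41.2% | 37.7% |
| 70% | 95.2% | 85.0% |
| 80% | 99.7% | 96.7% |

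Even ten patients give a rule that responds to the switch rate. The fault lies in the denominator, not in the small sample.

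**The case against.** The strongest reply is that the text allows another reading. The first 20 patients fix when the look takes place, but the threshold sentence does not repeat that denominator, whereas the protocol-violation rule in the same section does. If switches were counted among everyone included by then, the threshold could be reached. With 40 included, about 20 of them in the HandScan arm, it would be met 41% of the time at a 50% switch rate. That is an upper bound, because later patients have shorter follow-up. If 20 HandScan patients were meant, the rule would also work. Neither reading is stated, and the preceding sentence ties the count to the first 20. Someone applying the text literally gets a nearly inert rule, so under either alternative the wording still needs correction. The article condenses a fuller protocol that may be clearer, but this rule is printed here with both of its numbers.

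A second reply is that other safeguards exist. This is partly right: each discordant patient is switched automatically, and protocol violations in more than 20% of the first 20 patients are reported to the ethics committee and may lead to modifications. Neither stops inclusion, and neither measures how often HandScan guidance has to be abandoned.

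It is also true that the sample size, margin and primary test do not depend on this rule. Its effect is on whether a trial that has become uninformative would be recognized in time.

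**Conclusion.** The concern holds. On the plain reading, the rule fires with probability below 5% for any switch rate up to 80%, 12–14% at 90%, and 31–33% when every HandScan patient switches. It would therefore miss total failure of HandScan guidance about two times in three. These figures assume five or six recruiting centers, independent switching and an assumed range of switch rates. The structural point needs no assumed rate: with ten HandScan patients among the 20, the threshold is out of reach. Because this is the only rule in the article that stops inclusion, it must be corrected.

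**What to change.** State the denominator as HandScan-arm patients and set the threshold to match. There are two workable forms:

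1. Keep the look at the first 20 patients overall and stop inclusion if more than half of the HandScan-arm patients among them have switched. This adds no delay.
2. Keep the threshold of more than ten, and hold the look when the first 20 HandScan-arm patients have 6 months of data. This discriminates better, but needs about 40 randomized patients before the look, or 40/112 = 36% of the total given under Sample size.

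The first is the cheaper change. More than half is a proposal that follows the apparent intent of ten out of 20; the sponsor should confirm the fraction and record its firing probabilities. Either form takes one sentence in an amendment. The independent researcher must know which of the 20 patients are in the HandScan arm, and can report only whether the threshold was met, so site blinding is kept. The article says that recruitment is under way. If the look has already been held, the switch count should be reassessed against the number of HandScan-arm patients.

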### Implementation of a software application for patient-tailored, tight-control treatment

Although treatment regimens and dosing steps are identical for all patients, actual medication will differ considerably between patients in this study, as the study protocol tailors treatment to every patient in a treat-to-target strategy (Fig. 3). To account for these variations in treatments and to allow for double-blind treatment, a decision-making software application was developed. It uses a data trail (data log) of current and previous patient-specific input to check, e.g., for consistent discordance between remission criteria and prevent drug dosages higher than previous MTD in case of a flare. At each visit, the patient identification number, year of birth, and parameters for both clinically and HandScan-assessed disease activity will be entered into the application. Based on whether there is remission or not, according to the criteria of the randomized arm, the application will provide the next patient-specific medication step.

The application was developed and tested to conform to the regulations and guidelines for the development of a medical appliance class I and medical software class B (*EN 62304 Medical device software –Software life-cycle processes, EN 62366 Usability, ISO 14971 Medical devices – Application of risk management to medical devices*).

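### Adverse events are recorded, but a comparison between arms is ruled out on a premise that the protocol itself undercuts, leaving drug toxicity uncompared beside a non-inferior HAQ

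*Protocol article*

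**What the plan says.** The relevant statements are in three sections of the protocol article.

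- **Patient safety.** On collection: "All adverse events reported by trial participants or observed by investigator staff will be recorded". On analysis: "no safety analysis will be performed and an independent data safety and monitoring board will not be installed". The reason given is "As the study does not involve experimental medication or treatment". The exclusion carries no qualifier and is not confined to interim looks.
- **Implementation of a software application.** The guidance determines treatment: "according to the criteria of the randomized arm, the application will provide the next patient-specific medication step". The section also expects that "actual medication will differ considerably between patients in this study".
- **Prevention of under- and overtreatment in the HandScan arm.** The HandScan approach is called novel, and "measures are taken to prevent large deviation of the HandScan-guided strategy from the DAS guided strategy to avoid under- or overtreatment". After three consecutive discordant monthly decisions, "patients will be switched to the DAS-guided arm and medication decisions will be immediately guided by this arm".

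**The concern.** The reason for omitting a safety analysis looks at the drugs and not at what is randomised. The drugs and their steps are the same in both arms. Whether a patient is escalated, held or tapered at a visit depends on the remission criteria of the assigned arm, and these differ. Exposure to methotrexate, prednisolone, hydroxychloroquine and anti-TNF is therefore a consequence of randomisation.

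The trial sets out to show that HandScan guidance is no less effective and is more cost-effective, and the Discussion presents the software-guided treatment as safe. More drug can hold or improve HAQ while causing more adverse events. If one arm reached its HAQ result that way, the stated plan contains no comparison that would show the toxicity side. The direction is open. The Objectives section argues that DAS-based criteria tend to miss true remission, which could mean more drug in the DAS arm. A comparison by arm could therefore count in favour of HandScan as easily as against it.

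**Working it through.** **1. Does the premise fit the rest of the protocol?**

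| Premise or consequence | What the protocol states elsewhere |
|---|---|
| No experimental treatment, so no safety analysis | The guidance is novel and randomised, and sets the next medication step |
| Drugs and steps are identical in both arms | The step taken depends on the arm's own remission criteria (Definitions of remission) |
| Discordant decisions between methods | Expected, since a switch rule is built for them; the Background reports a correlation with DAS28 of only r = 0.42 |
| Overtreatment | Named as a risk, with measures against it |

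The premise is true of the drugs and untrue of the strategy under test.

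**2. Which harms does the plan compare by arm?**

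- Loss of function: yes, HAQ at 18 months and over time.
- Joint damage: yes, Sharp/van der Heijde total, narrowing and erosion scores.
- Quality of life: yes, SF36 and EQ5D.
- Amount of drug: indirectly, through the bootstrapped difference in drug cost.
- Adverse drug effects: no. They reach direct costs and utilities only in part, and a cost difference does not show which events occurred or how often.

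The gap is drug toxicity, the harm specific to overtreatment.

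**3. Do the safeguards fill the gap?** The switch rule and the independent count of switches in the first 20 patients measure disagreement between the two methods. The 20% trigger measures protocol violations. Neither compares adverse events between arms.

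**4. What precision would a comparison have?**

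The plan's own sample size first. With margin 0.2, SD 0.4, one-sided 0.05 and 80% power, the normal approximation gives n = 2 × (1.645 + 0.842)² × 0.4² / 0.2² = 49.5, so 50 per group. The noncentral t gives 51 (power 80.6%), which matches the stated 51. Adding 10% gives 102 × 1.1 = 112.2, against the stated total of 112, or 56 per arm.

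The documents give no adverse event rates, so the rates below are assumptions. For an equal rate p in both arms, the half-width of the 95% confidence interval for the difference is 1.96 × √(2p(1 − p)/n). At p = 0.10 and n = 56 this is 1.96 × √(0.18/56) = 0.111. The last column gives the rate in the other arm that would be detected with 80% power at two-sided 0.05, from a two-proportion normal approximation with pooled variance under the null.

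| Assumed proportion with event | 95% CI half-width, 56 per arm | Detectable rate in the other arm |
|---|---|---|
| 5% | 8.1 points | 23% |
| 10% | 11.1 points | 31% |
| 20% | 14.8 points | 45% |
| 40% | 18.1 points | 66% |

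The Abstract gives 61 per arm instead. The half-widths are then 7.7, 10.6, 14.2 and 17.4 points, and the conclusion is the same: estimates with intervals are feasible, while formal tests would find only large differences.

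**The case against.** The strongest defence is that the drugs are established, the steps are shared, and the named risk is already managed. Monthly dosage decisions take adverse events into account, blood is sampled at each visit to monitor for adverse effects, the application prevents doses above an earlier maximum tolerable dose in a flare, and persistent discordance triggers a blinded switch. This stands as protection of individual patients. It does not supply a comparison between arms.

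A second defence is that an article condenses the full protocol and that safety tables belong in an analysis plan. That would answer silence. Here the text rules the analysis out and gives a reason. The defence has more force for drug exposure: the exclusion does not mention exposure summaries, and an unseen plan may contain them. Exposure is therefore an accompaniment to the fix and not an omission in itself.

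Three stronger readings are tempting, and the documents do not support them.

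- **That harm from over- or undertreatment would go unreported.** Undertreatment harm is compared through HAQ, radiographs, SF36 and EQ5D, and extra drug use would partly appear in drug costs. The text excludes an analysis; it does not say that recorded events will be withheld.
- **That the size of the harm can be read from the treatment steps or the switch rule.** By Table 2, a patient never in remission reaches anti-TNF after six 4-week steps, at week 24, which leaves 78 − 24 = 54 of 78 weeks. That path is the same in both arms. The switch rule would also allow 12 of 18 monthly decisions to be discordant if two discordant visits were always followed by one concordant visit. This is a combinatorial ceiling with no stated likelihood. Neither figure measures a difference between arms.
- **That the lack of a monitoring board is the fault.** For marketed drugs with an independent early check this is a lesser matter, and the comparison needed does not depend on a board.

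**Conclusion.** The point holds in a limited form. The protocol records adverse events and positively excludes their analysis, on a premise contradicted by its own account of how the randomised guidance works. Drug toxicity is the one relevant harm without a planned comparison by arm. The primary analysis remains valid, but a non-inferior HAQ would be incompletely interpretable, because the reader could not see whether it came with more adverse events.

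No size can be put on a toxicity difference, nor its direction stated, because the documents give neither adverse event rates nor expected exposure by arm. What can be stated is precision: half-widths of about 8 to 18 percentage points with 56 per arm, for assumed proportions of 5% to 40%, equal rates in both arms and no allowance for dropout. That argues for a descriptive comparison and does not justify leaving it out.

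**What to change.** In Patient safety, delete the statement that no safety analysis will be performed and commit to the following:

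- a descriptive summary by randomised arm, in all randomised patients, of adverse events and serious adverse events: number and percentage of patients with an event, rate per patient-year, and the between-arm difference with a 95% confidence interval, without formal testing;
- patients switched from HandScan to DAS guidance stay in their randomised arm, so that the comparison is of the strategies as allocated, switch rule included;
- beside it, a by-arm summary of exposure to methotrexate, prednisolone, hydroxychloroquine and anti-TNF from the recorded medication data, stating whether the figures are doses advised by the application or doses taken, since clinical judgement may lead to departures from the advice.

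The cost is a few tables from adverse events already being collected and from whatever medication data are recorded. Treatment, visits and sample size do not change. The downside is low precision, above all for rare serious events, so the text should say beforehand that a wide interval or the absence of a visible difference is not evidence of equal safety. No monitoring board is needed for this.

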## Discussion

This study aims to evaluate clinical efficacy of a HandScan-guided versus DAS-guided tight-control and treat-to-target treatment strategy for early RA. The HandScan guidance has potential drawbacks, mainly because it relies solely on arthritic activity in hands and wrists. However, optical spectral transmission (OST) did correlate to DAS28 in a previous study [6], as well as to US assessed synovial inflammation of hand and wrist joints, while DAS28 did not correlate with these US results. It is possible that, considering the strengths and weaknesses of both guidance methods, the optimal guidance for future treatment of early RA would be using both methods or a combination of parameters of both methods (e.g., HandScan with CRP measurement).

An economic evaluation of guidance of a tight-control strategy using the HandScan has been previously published [17]. Implementation of the HandScan as a monitoring tool was modeled at comparable costs and comparable effects as using clinical assessments. To validate this result, cost-effectiveness in the current study will be calculated based on actual data (i.e., a trial-based economic evaluation); this approach requires less assumptions and therefore has a lower risk of bias.

This protocol describes a specifically designed software application to allow for double-blind, safe, and patient-tailored guidance of treatment. Implementation of the software application has the advantage that it allows for on-site patient randomization and double-blind (for the guidance method) treatment. Deviation from standard treatment schedules is allowed, for example, by defining a MTD or the opportunity to switch from MTX to LEF in case of MTX intolerance. Three consecutive discrepancies in medication advice between the HandScan and DAS arm lead to switch of the respective patients in the HandScan arm to the DAS arm as a built-in safety for potentially large differences between arms. Importantly, as neither the patient nor the physician is aware of a switch, the double-blind design will be maintained.

This specifically designed decision-making software application also allows for implementation of other RCTs testing future, novel methods of guidance of tight-control and treat-to-target treatment strategies in RA.

